**Estimation of sample size**

This study was a prospective exploratory study. Using PSQI as the primary outcome and intervention and control group allocated as 1:1). Estimation of sample size is based on the results of the preliminary study, the mean PSQI score of patients with chronic insomnia is 14.9 (SD, 4.3), and the PSQI score is expected to be reduced to 11.1 after 8-weeks of taVNS treatment. Considering the dropout and loss to follow-up rate of approximately 25%, and with 0.05  $\alpha$ -level and 90% power, the total sample size required for the trial is 72 patients.

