**Screening, randomization and blindness**

Eligible patients will be recruited from hospital outpatient clinics at Acupuncture and Moxibustion Hospital, China Academy of Chinese Medical Sciences (CACMS). If the recruitment could not reach the goal as the designed timetable frame at the end of the first year, additional study sites or other means of recruitment methods, such as advertisement, hospital WeChat official account and posters, will be considered to be included.

Screening will be conducted by the principal investigator following the inclusion and exclusion criteria. Randomization will be performed by an independent statistician in blocks with the use of SAS (version 9.4) software, with a block length of four. The randomized contents will be bound in closed envelopes,

and the order of each envelope is marked, which will be kept by a research assistant, but inaccessible to other study personnel. Remove envelopes according to the order in which the patients are enrolled.

After patient's eligibility is confirmed, patients will be randomly assigned to taVNS group or sham taVNS group in a ratio of 1:1 by informing as follows: "you will be randomly assigned to taVNS or sham taVNS treatment for your insomnia syndrome. You will have an equal chance to be assigned in either group, but either you or we will not know which group you will be assigned until investigational treatment completes." Clinical investigators, care providers, lab technicians, and data analysts will be blind to patients' treatment condition. The success of blinding will be tested by asking all participants the following question after the completion of the investigational treatment: "When you volunteered for the trial, you were informed that you had an equal chance of receiving taVNS or sham taVNS treatment. Which do you think you received?"

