### **Unblinding Procedures**

The study treatment blind shall not be broken by the investigator unless information concerning the

study treatment is necessary for the medical treatment of the subject. In the event of a medical emergency, if possible, the medical monitor should be contacted before the study treatment blind is broken to discuss the need for unblinding. For unblinding a subject, the study treatment blind can be obtained by the principal investigator. If any site personnel are unblinded, the dosing of the study treatment would be stopped immediately and the subject would be withdrawn from the study. The date, time, and reason the blind is broken would be recorded.

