#### **Treatment procedure**

The intervention protocol was based on a preliminary clinical trial, utilized an electroacupuncture instrument (Hwato, SDZ-II B, Suzhou, China) and special silica gel ear clips. Patients in both groups received electrical stimulation at the bilateral auricular cymba conchae(auricular point kidney, CO10) and cavum conchae(auricular point heart, CO15), where there is rich of vagus nerve distribution. Patients in taVNS group received stimulation parameters, including dilatational wave at 4/20Hz (4Hz for 5 seconds, 20Hz for 10 seconds, alternately), pulse width of 0.2ms±30%, and intensity adjusted to the patient's maximum tolerable level (0.8~1.5mA). The sham taVNS group received the same parameters with a current intensity of 0.1mA.

On the day of enrollment, each patient will be taught to use the instrument, informed of precautions, and ensure that each patient could treat himself at home. Patients in both groups start treatment on the day of randomization and bilateral auricles receive stimulation simultaneously for 30 min each time, twice a day, five consecutive days a week, for 8 weeks, followed by a 12-week observational period. Sleep treatment diary will be used to monitor the patient's treatment and sleep status.

Patients are encouraged to avoid using medications or other therapies for treatment of insomnia throughout the trial. In accordance with the Declaration of Helsinki, if patients have severe insomnia and affect their daily life, temporary use of sleeping pills is allowed (the frequency of continuous use of drugs is allowed to be less than 3 nights), and the name and dose of drugs are recorded in the sleep diary and informed to the responsible doctor. For those who were under anti-hyperlipidemic, antihypertensive and anti-diabetic treatment, they were allowed to continue their current medications throughout the study. Drug history of the participant will be systematically recorded in the case report form.

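### Whoever sets or teaches the current knows the arm, despite the claim that investigators and care providers are blind; with a fixed block of four, leaked arms make later allocations predictable

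*Protocol*

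**What the plan says.** Protocol, Screening, randomization and blindness, makes a broad claim: "Clinical investigators, care providers, lab technicians, and data analysts will be blind to" each patient's allocation. Patients are told that neither they nor the study team will know the group until treatment ends. The same section says that randomisation is in blocks, "with a block length of four", and that "patients will be randomly assigned to taVNS group or sham taVNS group in a ratio of 1:1". No stratification is mentioned. A research assistant keeps the numbered envelopes, and no one else on the study has access to them. On entry: "Screening will be conducted by the principal investigator following the inclusion and exclusion criteria".

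Protocol, Treatment procedure, gives the current in each arm. In the active arm it is raised to the most the patient can tolerate, within 0.8 to 1.5 mA. For sham: "The sham taVNS group received the same parameters with a current intensity of 0.1mA". Each patient is taught the device on the day of enrolment and then treats at home. The section does not say who sets the current or who teaches. It describes no masked or pre-programmed device.

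Protocol, Unblinding Procedures, allows the blind to be broken only for a subject's medical care. In that case, "the study treatment blind can be obtained by the principal investigator". It adds that if any site personnel become unblinded, study treatment stops at once and the subject is withdrawn.

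**The concern.** Titrating one patient to tolerance and setting another at 0.1 mA are visibly different acts. The person who does either one, or instructs the patient in it, knows the arm. The protocol nevertheless counts all investigators and care providers as blind, and assigns the task to nobody outside those groups.

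Two biases are possible:

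- **Detection bias.** The Hamilton depression and anxiety scales are secondary outcomes. The text does not keep the operator away from rating them.
- **Selection bias.** If arms become known to the person who screens, a fixed and stated block length turns past arms into knowledge of future ones. Entry depends on score windows (PSQI of at least 8, HAMA 7 to 14, HAMD 7 to 17). Foreknowledge at screening could therefore affect the primary PSQI comparison and not only the secondary scales.

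The plan's own check would not reveal either problem. Bang's index, as described, uses participants' guesses only, so staff unblinding would go unmeasured and the trial would still be reported as blind.

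**Working it through.** **The three sections side by side**

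| Protocol section | What it implies |
|---|---|
| Screening, randomization and blindness | Investigators and care providers do not know the arm |
| Treatment procedure | The arm can be read from the current: 0.1 mA against 0.8 to 1.5 mA, so at least an eightfold difference (0.8 / 0.1 = 8) |
| Unblinding Procedures | If site personnel know the arm, treatment stops and the subject is withdrawn |

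If site personnel set the current, the first two rows conflict unless the operator belongs to none of the groups listed as blind. The third row, taken literally, would then apply to every subject set up in this way. If the patient sets the current, someone must still give instructions that differ by arm, and the same problem returns.

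**Number of blocks**

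The only stated figure needed is the total: "the total sample size required for the trial is 72 patients". It reproduces. The inputs from Estimation of sample size are a difference of 14.9 − 11.1 = 3.8, SD 4.3, two-sided α 0.05, power 90% and 25% dropout:

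- n per arm = 2 × (4.3 × (1.960 + 1.282) / 3.8)² = 26.9, rounded up to 27
- 27 / (1 − 0.25) = 36 per arm, 72 in total
- 72 / 4 = 18 blocks

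**Allocations that can be deduced**

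Assume that the block length and all earlier allocations in the block are known. An allocation is certain once one arm has used both its places. The six equally likely orderings give:

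| Ordering | Certain allocations |
|---|---|
| AABB | 2 |
| ABAB | 1 |
| ABBA | 1 |
| BAAB | 1 |
| BABA | 1 |
| BBAA | 2 |

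- Mean: (2 + 1 + 1 + 1 + 1 + 2) / 6 = 8/6 = 4/3 per block, and (4/3) / 4 = 33.3%
- Over the trial: 18 × 4/3 = 24 of 72
- Possible range: 18 × 1 = 18 (25%) to 18 × 2 = 36 (50%)
- Distribution: 18 + Binomial(18, 1/3), with a central 95% range of 20 to 28 and a 39% chance of more than 24

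**Best-guess accuracy under the same assumption**

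- Place 1: 1/2
- Place 2: 2/3
- Place 3: 1/3 × 1 + 2/3 × 1/2 = 2/3
- Place 4: 1
- Average: (0.5 + 0.667 + 0.667 + 1) / 4 = 70.8%, against 50% by chance

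**Sensitivity to block length**

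Under the same full knowledge, fixed blocks of six leave 25.0% certain and fixed blocks of eight leave 20.0%. A longer block therefore helps only in part if arms leak. If no earlier arm is known, no allocation is certain at any of these lengths.

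**The case against.** The strongest reply is that the protocol never says who sets the current. Research assistants are not among the staff listed as blind, and one of them already holds the envelopes. The text is therefore compatible with that person being an unblinded operator, while the principal investigator screens blind. On this reading, concealment holds and a block of four does little harm. Part of this stands: the text does not prove that an investigator or care provider sets the current. But the operator role is unassigned, nothing separates it from rating or from contact with the screener, and a research assistant could still count as site personnel under Unblinding Procedures.

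A reader might infer three stronger points that the document does not support:

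- **That the principal investigator's access to the blind produces the predictability.** That access is for a single subject and for medical need. The medical monitor is contacted first where possible, and the date, time and reason are recorded. It is not access to the list, and an emergency exception does not contradict restricted envelopes.
- **That raters of the Hamilton scales are known to be unblinded.** No section says who rates them or that raters teach the device. This is an open risk only.
- **That one third is a ceiling, or applies regardless of what staff know.** It is an average, and it requires knowledge of the block length and the earlier arms.

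It is also fair to say that varying the block size is a secondary measure. If every arm leaked, it would reduce the predictability but not remove it. Separating the roles matters more.

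**Conclusion.** The point holds as an internal conflict in the protocol. The blanket statement of staff blinding cannot be squared with the stimulation procedure unless an unblinded operator exists, and none is named. Read literally, the unblinding rule would then reach subjects whose current was set by site personnel. The sections on blinding, treatment and unblinding must be reconciled.

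The fixed block of four adds to the exposure. On average 33.3% of allocations (24 of 72; possible range 25% to 50%) are certain in advance, with 70.8% guessed correctly. These figures assume two allocations per arm in each block, no stratification, and a person who knows the block length and every earlier arm in the block. The protocol does not show that anyone who screens would have this knowledge, but it does not prevent it either. No size can be put on any resulting bias in PSQI, HAMD or HAMA from the document.

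**What to change.** 1. Use randomly varying block sizes, for example 4 and 6, and keep the block lengths out of the protocol given to site staff.
2. Name one existing team member, such as the research assistant who holds the envelopes, as the unblinded operator. This person sets and teaches the device, takes no part in screening or scale rating, and does not disclose the arm.
3. Restrict the staff blinding claim to screeners, raters and analysts, and reconcile Unblinding Procedures with the existence of an unblinded operator. How that rule should read is for the sponsor to decide; the sections only need to agree.

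The cost is a new randomisation list and revised wording of roles, with no added patients or visits. The statistical price is a slightly larger possible imbalance between arms at the end of the list.

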### **Unblinding Procedures**

The study treatment blind shall not be broken by the investigator unless information concerning the

study treatment is necessary for the medical treatment of the subject. In the event of a medical emergency, if possible, the medical monitor should be contacted before the study treatment blind is broken to discuss the need for unblinding. For unblinding a subject, the study treatment blind can be obtained by the principal investigator. If any site personnel are unblinded, the dosing of the study treatment would be stopped immediately and the subject would be withdrawn from the study. The date, time, and reason the blind is broken would be recorded.

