## **Data analyses**

The analysis will be performed on the intention-to-treat (ITT) population that participants had been randomized. All efficacy analyses will be performed using the ITT analysis set and PP analysis set, defined as all randomized participants who received at least 6-week intervention. A mixed model for repeated measures (MMRM) with likelihood-based modeling to handle missing data will be applied to compare the primary outcome and secondary outcomes: change in the PSQI, ISI, HAMD, HAMA, ESS, FFS scores from baseline to week 4, 8, and 20. The model includes terms for treatment (taVNS or sham taVNS), visit (weeks 4, 8, 20), treatment by visit interaction, and baseline scores. Least squares mean change from baseline and least square mean difference between the groups at week 8 along with 95% confidence interval and a 2-sided p value will be estimated for the primary end point. Cohen d effect size will be calculated using the absolute value of the least square mean difference between groups in score from baseline at week 8 divided by the pooled SD estimated from the mixed model for repeated measures. For the PSQI responder analysis, the responder is defined as a 50% decrease at the end of treatment compared with baseline, which is prespecified in the statistical analysis plan. The percentage of PSQI responder at week 4, 8 and 20 will be calculated and summarized by treatment group. The percentage of PSQI responders at week 8 and 20 will be compared between groups using the Chi-square test. SAS, version 9.4 (SAS Institute Inc) is used for all analyses, with significance set at  $P < 0.05$ .

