## **Criteria for Discontinuation or Withdrawal of a Subject**

(1) Pretreatment event or AE: The subject has experienced a pretreatment event or AE that requires early termination because continued participation imposes an unacceptable risk to the subject's health or the subject is unwilling to continue because of the pretreatment event or AE. (2) Major protocol deviation: The discovery post-randomization that the subject failed to meet protocol entry criteria or

316 did not adhere to protocol requirements, and continued participation poses an unacceptable risk to the  
317 subject's health. (3) Lost to follow-up: The subject did not return to the hospital and attempts to contact  
318 the subject were unsuccessful. (4) Withdrawal of consent: The subject wishes to withdraw from the  
319 study. (5) Study termination: The principal investigator, IRB, REC, or regulatory agency terminates the  
320 study.

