### 321 322 **Procedures for Discontinuation or Withdrawal of a Subject**

323 The investigator may terminate a subject's study participation at any time during the study when the  
324 subject meets the study termination criteria. In addition, a subject may discontinue his or her  
325 participation without giving a reason at any time during the study. Should a subject's participation be  
326 discontinued, the primary criterion for termination would be recorded. Subjects who discontinue the  
327 study during the double-blind treatment period will visit the site as soon as possible for clinical  
328 assessment if applicable. Discontinued or withdrawn subjects will not be replaced.

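### Subjects are withdrawn from the study when staff are unblinded, and no week-8 or week-20 assessment is stated after discontinuation, which conflicts with an analysis of all randomised participants

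*Protocol*

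**What the plan says.** Unblinding Procedures restricts breaking the blind to cases where information about the "study treatment is necessary for the medical treatment of the subject". If any site personnel are unblinded, the consequence is fixed: "the dosing of the study treatment would be stopped immediately and the subject would be withdrawn from the study".

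Criteria for Discontinuation or Withdrawal of a Subject gives a single list for both events: adverse event, major deviation, loss to follow-up, withdrawn consent and study termination. The adverse-event item covers an event that "requires early termination because continued participation imposes an unacceptable risk" to health, or a subject who does not wish to go on because of it. The list has no separate status for a subject who has stopped stimulation but is still being assessed.

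Procedures for Discontinuation or Withdrawal of a Subject says that those who discontinue during the double-blind period "will visit the site as soon as possible for clinical" assessment, where that applies. It adds: "Discontinued or withdrawn subjects will not be replaced". It does not mention the week-8 or week-20 assessments for these subjects.

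Data analyses states: "The analysis will be performed on the intention-to-treat (ITT) population that participants had been randomized". The model is a likelihood-based MMRM with visits at weeks 4, 8 and 20, and the primary comparison is at week 8. The per-protocol set is "defined as all randomized participants who received at least 6-week intervention".

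**The concern.** An analysis of all randomised participants needs outcomes from all of them as far as possible, including those whose treatment or blinding went off plan. Here a rule written into the protocol removes a randomised subject because of something that happened after randomisation. The neighbouring sections then state no scheduled follow-up for subjects who discontinue. Such a subject stays in the ITT set but may have no week-8 score.

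The MMRM handles that gap by assuming missing at random. In effect, the unobserved week-8 change is predicted from subjects in the same arm with a similar observed history, most of whom will have continued treatment. If those who left would have done worse or better than that prediction, the estimated treatment difference is biased to the extent that the departure is unbalanced between arms.

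This has to be settled in the protocol. A statistical analysis plan can choose models and sensitivity analyses, but it cannot recover scores that site procedures never collected.

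**Working it through.** **Step 1: the sections side by side.**
- Unblinding Procedures: unblinding of site staff leads to withdrawal from the study. This is an explicit rule.
- Discontinuation and withdrawal sections: one list for both events, one early visit where applicable, no replacement, and no statement on weeks 8 and 20.
- Data analyses: all randomised participants, modelled at weeks 4, 8 and 20.

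The first two, followed as written, do not supply the data that the third assumes.

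**Step 2: the plan's own sample size.** Inputs from Estimation of sample size: PSQI mean 14.9, SD 4.3, expected 11.1 after taVNS, alpha 0.05, power 90%, 25% loss. Data analyses makes the test two-sided.
- Difference = 14.9 − 11.1 = 3.8.
- n per arm = 2 × 4.3² × (1.960 + 1.282)² / 3.8² ≈ 26.9, rounded up to 27.
- Inflated for loss: 27 / 0.75 = 36 per arm, 72 in total.

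The stated 72 is reproduced (normal approximation). The planned loss of precision is therefore already allowed for, and the open question is bias. The 3.8 is an expected change within the taVNS group. It acts as a between-arm difference only if sham does not change, and it is used below on that footing.

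**Step 3: a formula for the bias.** Let w be the fraction of an arm with no week-8 outcome. Let d be how much worse, in PSQI points, those subjects' true change is than the model implies. Then

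bias in favour of taVNS = w(active) × d(active) − w(sham) × d(sham).

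The protocol gives none of these four quantities, so every value below is an assumption.

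| Scenario | Calculation | Bias (points) |
|---|---|---|
| One active patient of 36 unblinded, all benefit lost, sham missing at random | 3.8 / 36 | 0.11 |
| 5% of active arm lost, half of benefit lost, sham missing at random | 0.05 × 1.9 | 0.10 |
| 25% of active arm lost, half of benefit lost, sham missing at random | 0.25 × 1.9 | 0.48 |
| 25% of active arm lost, all benefit lost, sham missing at random | 0.25 × 3.8 | 0.95 |
| Equal rates and departures, e.g. 25% and 3.8 in both arms | 0.25 × 3.8 − 0.25 × 3.8 | 0 |
| 10% active, 25% sham, departure 3.8 in both | 0.10 × 3.8 − 0.25 × 3.8 | −0.57 |

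Relative to 3.8, the first row is 1/36, about 3%, and the 0.95 row is 25%. The last row shows that the sign can reverse.

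**Step 4: precision.** With 27 observed per arm, power is 90.1%; with all 36 observed it is 96.3% (normal approximation). Some of the planned loss would occur whatever the rules say, so 96.3% is a ceiling on what continued follow-up could achieve.

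**The case against.** Several stronger readings are tempting, and the protocol does not support them.

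*That stopping stimulation ends participation.* A reader might infer this from the merged sections, but no section states it. Simply stopping stimulation is not on the list of criteria, the procedures say that the investigator may end participation, and poor compliance is recorded without being a ground for withdrawal. The per-protocol definition also implies that the ITT set can hold people who stopped before six weeks. This objection stands. It does not remove the point, because belonging to the ITT set does not supply a week-8 score.

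*That 0.95 points measures the defect.* It does not. The allowance is worded "Considering the dropout and loss to follow-up rate of approximately 25" per cent, and part of it (loss to follow-up, withdrawn consent) would be lost under any wording. Unblinding is permitted only for medical need and is probably rare, so on its own it belongs near the 0.1 end.

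*That the bias favours taVNS.* One might expect more tolerability losses at the maximum tolerable current (0.8 to 1.5 mA) than at 0.1 mA. That is plausible, but the protocol gives no rates or reasons by arm. Sham patients may equally leave for lack of effect, which pushes the other way.

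*That the analysis is not ITT at all.* Withdrawn subjects remain in the randomised set and the MMRM uses their earlier visits. Anyone who leaves after week 8 has already given the primary outcome. Visit windows and sensitivity analyses commonly sit in a statistical analysis plan, so it cannot be said that the early-visit score has no place in the model.

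*That anyone who sets the current counts as unblinded and triggers withdrawal.* The rule appears in a section on breaking the blind for medical need. Who can see the current is a separate question about blinding.

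**Conclusion.** The point holds in limited form. Withdrawal from the study on unblinding is an explicit rule, and the discontinuation sections state no week-8 or week-20 assessment. Both conflict with the stated analysis of all randomised participants, and both make the primary result depend more on missing at random than it needs to.

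The size and direction of any bias cannot be determined from the protocol. On the assumptions shown, a single unblinded active patient moves the estimate by about 0.1 PSQI points and the upper scenario is 0.95. Balanced losses with equal departures give zero, and heavier sham losses could reverse the sign. All these figures treat 3.8 as the between-arm difference. The sample size is not affected.

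**What to change.** Reconcile Unblinding Procedures, the two sections on discontinuation and withdrawal, and Data analyses on one matter: whether outcomes are still collected. State that unblinding or discontinuing treatment does not by itself end outcome collection. Unless consent is withdrawn or the subject cannot be reached, PSQI and the other scales are still collected at weeks 4, 8 and 20, remotely for the self-report scales if needed, and these scores enter the ITT MMRM. Record the date of stopping or unblinding and the reason, so that losses can be reported by arm.

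The cost is about three sentences and a few extra scale completions. Whether and when treatment stops, and the safety grounds for discontinuation, are clinical rules that this change leaves as they are.
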